### Statistical analysis

Statistical analysis will be conducted with the assistance of the Clinical Trials Unit of La Paz University Hospital. To analyse the continuous variables, the following information will be collected: the number of participants, mean, SD, median, minimum, maximum and 25th and 75th percentiles. For the categorical variables, the frequency distribution and 95% CI will be provided.

Multivariate logistic regression analyses will be performed to evaluate the effect of glucose levels at the time of reperfusion on functional recovery at 3 months, adjusting for other factors that show statistically significant differences in the univariate analysis. Significance will be assessed using the likelihood ratio.

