## Introduction

 Poststroke hyperglycaemia is a very common complication in ischaemic stroke, affecting approximately two-thirds of patients, and is associated with poorer recanalisation rates, reduced perfusion, increased damage due to ischaemia-reperfusion and, consequently, poorer patient outcomes.^1 2^ Furthermore, hyperglycaemia can counteract the potential therapeutic effect of reperfusion treatments such as intravenous thrombolysis^3 4^ and mechanical thrombectomy (MT).^5^,^8^

Hyperglycaemia can cause damage through several pathophysiological mechanisms, including abnormalities in the blood–brain barrier and increased lactic acid production.^1 2^ Poststroke hyperglycaemia has been independently associated with poor outcomes after MT, with lower rates of functional recovery,^6 7 9^ a higher risk of haemorrhagic transformation^7 9 10^ and cerebral oedema^11 12^ and increased mortality at 3 months.^7^ The GLycemia in Acute Stroke (GLIAS) study was the first multicentre study to establish prognostic threshold for hyperglycaemia at 155 mg/dL, demonstrating a correlation between elevated glucose levels in the acute phase of stroke and poor outcomes, independently of stroke severity, infarct volume, diabetes or age.^13^

In patients treated with MT, the Solitaire Flow Restoration With the Intention for Thrombectomy (SWIFT) clinical trial showed that for each 10 mg/dL increase in blood glucose values, there was a 42% reduction in the probability of an excellent recovery at 3 months.^6^ It has yet to be determined whether administering insulin therapy prior to and during MT can mitigate the negative impact of hyperglycaemia in stroke recovery. Several studies have attempted to analyse this impact based on retrospective discrete determinations, such as glycaemia on admission^5 7 8 14^ and 24–48 hours after stroke,^15^,^17^ but none of them have monitored glycaemia during the MT procedure.

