These miRNAs are of interest due to their functions, with previous studies demonstrating a role in cerebral ischaemia. In the context of ischaemic stroke, miR-339, miR-15a, miR-424 and miR-100 have been associated with large vessel occlusion.^33 34^ MiR-339, which is overexpressed in cases of cerebral and myocardial ischaemia,^35^ is related to neuronal survival and suppression of apoptosis in ischaemic conditions.^36^ MiR-15 and miR-424 have been linked to an antiangiogenic effect through VEGF inhibition.^37^ Additionally, miR-100 has been demonstrated to have an antiatherosclerotic effect.^38^ Furthermore, this miRNA exhibits varying levels in patients with cerebral infarction due to large vessel occlusion, suggesting a potential association with functional recovery.^33^ Finally, miR-29b has been demonstrated to attenuate ischaemic injury by negatively regulating the p53-dependent apoptosis pathway and could, therefore, be a potential target in diminishing cell injury in ischaemic stroke.^39^

We hypothesised that those patients with glycaemia values <155 mg/dL during MT and especially at the time of reperfusion will have less ischaemia-reperfusion injury, showing a different miRNA expression profile, with better neurological and functional outcomes and a lower risk of haemorrhagic transformation and cerebral oedema.

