#### Primary endpoints

Stroke recovery at 3 months was measured by the dichotomised mRS (0–2 indicating good functional recovery and 3–6 indicating death or dependency).

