#### Data collection and management

Glucose levels at the time of reperfusion in patients achieving thrombolysis in cerebral infarction (TICI) -2b, TICI-2c or TICI-3 recanalisation pattern after MT.mRS at 3 months. Its dichotomised assessment (mRS 0–2 indicating good functional recovery and 3–6 indicating death or dependency) is commonly used in acute stroke trials.Related to glycaemic control:Peak interstitial glucose levels during the MT procedure.Total time with interstitial glucose levels above 155 mg/dL from arrival in the emergency department to arterial recanalisation.Time with interstitial glucose levels in the range of 110–154 mg/dL: (a) from arrival at the emergency department to recanalisation; (b) during the first 24 hours and (c) during hospitalisation.Proportion of patients receiving insulin therapy for poststroke hyperglycaemia during the first 24 hours after onset of stroke symptoms.Insulin therapy received in clinical practice (time, route and dose).Number of CGMs with technical failures (missing or interrupted readings) or requiring replacement due to involuntary device removal or inadequate implantation.Additional CGM device data: mean interstitial glucose level, coefficient of variation.Related to MT:The number of MT passes (including aspiration and stent retriever passes).Degree of recanalisation according to TICI classification on final angiogram.Blood pressure in the emergency department and at the time of reperfusion.Related to stroke:Infarct size at 24 hours (assessed by a neuroradiologist who will be unaware of the glucose monitoring data).Haemorrhagic transformation at 24 hours (assessed by a neuroradiologist who will be unaware of the glucose monitoring data) is categorised into four types: (1) haemorrhagic infarction type 1 (HI-1)—small petechiae at the edges of the infarct area; (2) HI-2—confluent petechiae in the infarct area without mass effect; (3) parenchymal haematoma type 1 (HP-1)—haematoma occupying ≤30% of the infarct area with discrete mass effect and (4) parenchymal haematoma type 2 (HP-2)—haematoma occupying >30% of the infarct area with obvious mass effect.Symptomatic haemorrhagic transformation is defined as CT/MRI evidence of any type of haemorrhage associated with neurological deterioration ≥4 points on the NIHSS scale from baseline or leading to death.NIHSS score at 24 hours, at hospital discharge and at 3 months.Neurological or systemic complications during follow-up. The following complications will be systematically assessed at each visit: coma, seizures, early neurological deterioration, cerebral oedema, recurrent stroke, acute coronary syndrome, pulmonary thromboembolism, respiratory infection, urinary tract infection, sepsis and local haematoma or infection at the insertion site of the subcutaneous glucose monitor. Any other complication reported or detected during follow-up will be also recorded.Distribution of mRS scores at 90 days.Mortality at 3 months.Biomarkers of ischaemia-reperfusion injury: miR-29b, miR-339, miR-15a, miR-100 and miR-424. Samples will be drawn at the time of reperfusion and 24 hours later.Demographics: age, sex, race, weight, height, diabetes, hypertension, dyslipidaemia, coronary disease, atrial fibrillation, metabolic syndrome, chronic kidney disease with an estimated Glomerular Filtration Rate (eGFR)<60 mL/min/1.73 m^2^, smoking and alcohol abuse.Previous drug therapy: antiplatelets, anticoagulants, antihypertensives, antidiabetics and lipid-lowering agents.Stroke data: date of symptom onset (or last asymptomatic event in patients with unknown stroke onset), aetiological subtype of stroke and treatment with intravenous thrombolysis.Vital signs and laboratory values on admission at the emergency department: temperature, blood pressure, heart rate, respiratory rate, blood glucose and glycated haemoglobin.Treatment times: time from stroke onset to hospital admission; time from hospital admission to start of intravenous thrombolysis (door-to-needle time); time from hospital admission to start of MT (door-to-femoral puncture time); time from hospital admission to reperfusion; time from femoral puncture to reperfusion.Neuroimaging data: Baseline Alberta Stroke Programme Early CT Score, baseline collateral flow and baseline perfusion.

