#### Sample size estimates

There have been no previous studies using CGM devices to assess the dynamics of glucose levels in patients treated with MT, which would allow a formal calculation of the sample size. Furthermore, the proportion of patients in whom technical failures may impede the recording of glycaemia at the time of reperfusion remains unknown. Using previous studies,^29 30^ if we consider a 15% loss to sensor failure or loss to follow-up, we can calculate, with an alpha risk of 0.05, a beta risk of 0.20 and an estimated difference in death-dependence of 30%, that it is recommended a sample size of 50 patients per group be used, taking into account that the death-dependence ratio in the control group might be 0.66 (according to GLIAS-II data). However, given that the actual percentage of possible technical failures of the sensor is unknown, we propose to perform an intermediate analysis and recalculate the sample size after the inclusion of 50 patients. The inclusion of 100 patients over a 2-year recruitment period is considered feasible, given that the number of MT procedures in our centre exceeds 100 per year. This sample size will allow us to investigate the differences in glycaemic levels at the time of reperfusion between patients with good or poor functional recovery at 3 months. After enrolling 100 patients, further power calculations will be performed to estimate the sample size for future studies. Recruitment began on 30 August 2023 and is ongoing.

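### The only primary-endpoint model picks its covariates by univariate significance, so confounders can drop out by chance and variables measured after reperfusion are not barred

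*Protocol article*

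**What the plan says.** The Statistical analysis section of the protocol article plans multivariable logistic regression "to evaluate the effect of glucose levels at the time of reperfusion on functional recovery at 3 months". For the choice of covariates it gives a single rule, namely "adjusting for other factors that show statistically significant differences in the univariate analysis". The section does not label this model primary, but it is the only model given for the primary endpoint, the dichotomised mRS at 3 months.

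Three other places bear on the rule:

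- The Introduction reports that the earlier multicentre GLIAS study found its glucose association "independently of stroke severity, infarct volume, diabetes or age". The present plan guarantees adjustment for none of these.
- The hypothesis at the end of the Introduction is that patients with lower glucose will have less reperfusion injury, "with better neurological and functional outcomes and a lower risk of haemorrhagic transformation and cerebral oedema".
- Data collection and management lists true baseline variables (age, diabetes, glycated haemoglobin, baseline ASPECTS, collateral flow) together with variables measured after reperfusion: 24-hour infarct size, 24-hour haemorrhagic transformation, complications, and "NIHSS score at 24 hours, at hospital discharge and at 3 months".

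**The concern.** In a non-randomised study the adjustment set is the main protection of the glucose estimate against confounding. Here it is decided by p-values in the same small sample, and this can go wrong in two directions.

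1. A real confounder may not reach significance on its own in a sample of this size. It is then left out, and its effect is credited to glucose.
2. The wording sets no time limit on the eligible factors. Variables that lie between glucose and 3-month outcome predict that outcome strongly and would pass a significance screen easily. Adjusting for them removes part of the effect the study wants to estimate.

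The Discussion sets out to show that hyperglycaemia at recanalisation is a critical modifiable prognostic factor. That claim rests on which variables are in this model.

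**Working it through.** **Inputs from the document (Sample size estimates).** 100 patients, 15% loss, alpha 0.05, power 0.80, death or dependency 0.66 in the control group, difference 30%. Sidedness is not stated; two-sided is assumed. The 30% is read as absolute, giving 0.66 versus 0.36.

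**The plan's own figure.** With mean rate 0.51:

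n = [1.96·√(2·0.51·0.49) + 0.842·√(0.66·0.34 + 0.36·0.64)]² / 0.30² = (1.386 + 0.568)² / 0.09 ≈ 42.4, so 43 per group.

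Inflation for 15% loss gives 43/0.85 = 51 or 43 × 1.15 = 50. The stated 50 per group reproduces and is not at issue.

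**Evaluable sample.** 100 × 0.85 = 85. With half the patients in each group, the smaller outcome class is 85 × 0.49 ≈ 42. If the poor-outcome rate were 0.66 throughout, it would be 85 × 0.34 ≈ 29.

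**Chance that a true confounder fails the screen.** The document gives no confounder strengths, so these are assumed. The univariate comparison is taken to be against 3-month outcome. For one standardised covariate, the information is about 85 × 0.51 × 0.49 = 21.2, with root 4.61. The chance of missing p < 0.05 is therefore about Φ(1.96 − 4.61 × log OR). Simulation used likelihood-ratio tests at 0.05.

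| OR per SD | Formula, n=85 | Simulated, n=85 | Simulated, n=100 |
|---|---|---|---|
| 1.3 | 77% | 77% | 74% |
| 1.5 | 54% | 55% | 50% |
| 1.8 | 23% | 25% | 20% |
| 2.0 | 11% | 15% | 10% |

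Across all scenarios at n=85, including those with several confounders, the loss was about 54–71% at OR 1.5 and 14–22% at OR 2.0–2.2. With four confounders of OR 1.5, at least one was lost in 98% of samples.

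**False-positive rate for glucose, n=85, no true effect.** Assumed correlation of each confounder with glucose is 0.2–0.3 (0.2–0.35 in the last row). Some scenarios add 25 irrelevant candidates.

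| Assumed confounders | Screened | Same set prespecified |
|---|---|---|
| One, OR 1.3–2.0 | 0.052–0.072 | 0.047–0.065 |
| Two, OR 2.0 | 0.056–0.074 | 0.048–0.063 |
| Two of OR 2.2, one of 1.3 | 0.064–0.085 | 0.053–0.067 |
| Two of OR 2.2, two of 1.5 | 0.079–0.119 | 0.053–0.067 |
| Four of OR 1.5 | 0.089–0.150 | 0.055–0.068 |
| Four or five, log-OR 0.4–0.8 | 0.108–0.191 | 0.059–0.065 |

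For four confounders of OR 1.5 at correlation 0.3, the median spurious log-OR for glucose is 0.23 per SD (OR e^0.23 ≈ 1.26), against 0.00 with all four included. At correlation 0.2 it is 0.14 (OR ≈ 1.15).

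**If a post-reperfusion mediator enters.** Assume a glucose–mediator correlation of 0.4, a mediator log-OR of 1.2 per SD and a direct glucose log-OR of 0.3. On the linear-predictor scale the total effect is 0.3 + 0.4 × 1.2 = 0.78, of which 0.48 runs through the mediator. The mediator passes the screen in about 100% of samples. The median glucose log-OR falls from 0.65 to 0.32, and power from 0.78–0.79 to 0.19–0.21. With two mediators under different assumptions, power fell from 0.69 to 0.08. Part of this fall is a change of question: the adjusted model estimates a direct effect, not the total one.

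**The case against.** The strongest reply is that the article does not list the screening candidates, and such a list is the kind of detail a fuller document holds. The data-collection section is an inventory, not a candidate list. It also contains 3-month mRS and mortality, which cannot sensibly be covariates for 3-month mRS. The Secondary endpoints section treats 24-hour infarct volume, haemorrhagic transformation and NIHSS as outcomes. A reader might infer that the rule will pull mediators into the model. The text does not support that; it supports only that nothing in the wording keeps them out. This part of the reply stands.

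Two further inferences also fail. A reader might conclude that baseline NIHSS is not collected, because the NIHSS item starts at 24 hours. But symptomatic haemorrhage is defined by NIHSS change from baseline, and the schedule figure, whose legend includes NIHSS, is not available here. A reader might also count insulin in the first 24 hours as a post-reperfusion variable. The article counts that window from symptom onset, so it can include insulin given before reperfusion.

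The reply is also right that the error inflation depends on the assumptions. With one or two confounders it is slight or absent, and strong confounders usually survive the screen.

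Finally, this is a single-centre observational study that acknowledges possible bias and small size, and its results will feed power calculations for later studies. That lowers the severity. It does not rescue the rule, which the article states outright and so does not leave to an unseen analysis plan.

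**Conclusion.** The point holds in this form: for the only stated model of the primary endpoint, univariate significance is the sole entry criterion, no confounder is protected, and variables measured after reperfusion are not excluded.

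Its size is a range. The false-positive rate for glucose goes from no material inflation with one or two confounders to roughly threefold in the worst scenario with four or five (0.191 against 0.065). Quoting only the upper end would overstate it. The loss of power through mediators is conditional on their being admitted, which the wording permits but does not state. All these figures rest on assumed confounder strengths and correlations and on about 85 evaluable patients.

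This should be fixed before outcome data are analysed. It does not affect the planned sample size.

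**What to change.** In the Statistical analysis section, replace the univariate rule with a short set of pre-reperfusion covariates, fixed before outcome data are analysed and kept in whatever their p-values. One example is age, baseline NIHSS, diabetes or HbA1c, baseline ASPECTS and onset-to-reperfusion time (the sum of two intervals already collected). Infarct size as collected here is a 24-hour measure, so baseline ASPECTS is the pre-reperfusion counterpart.

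Add one sentence saying that no variable measured after reperfusion enters this model. Any analysis adjusting for such variables should be labelled as a separate, mediation-type question.

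Four or five covariates plus glucose make 5 or 6 parameters. That is 42/5 ≈ 8 or 42/6 = 7 patients in the smaller outcome class per parameter, so the set should not grow beyond this. If the smaller class is nearer 29, the shorter set is preferable. A penalised (Firth) fit as a sensitivity analysis is optional.

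The cost is one paragraph of wording and a registry update. A few degrees of freedom may go to covariates that prove unimportant. Recruitment targets are unaffected.

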## Discussion

This study represents a further step in the consolidated research into the prognostic impact of hyperglycaemia after stroke that began with the GLIAS study, the first prospective multicentre study to show that the glycaemic threshold associated with poor prognosis in acute stroke patients is 155 mg/dL.^13^ The GLIAS study also helped to highlight the significance of identifying and treating persistent hyperglycaemia.^40^ The GLIAS-II study (PS09/01781), funded by the Carlos III Health Institute (ISCIII), demonstrated the high incidence of non-response to conventional glycaemic control in patients with acute stroke and its association with poor outcomes.^18^ The GLIAS-III study (PI18/00991), currently finished and undergoing data analysis, is a multicentre, translational study analysing the impact of glycaemic variability evaluated by CGM on the progression of cerebral infarction in patients and in an animal model.^41^

The GLIAS-MT study aims to demonstrate that the impact of hyperglycaemia at the time of recanalisation is a critical modifiable prognostic factor, associated with greater brain damage, a different miRNA expression profile as a biomarker of damage, and poorer neurological and functional outcomes.

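### The aim singles out glucose at recanalisation, but the model does not prespecify admission glucose as covariate or comparator, so a significance screen decides what the reperfusion coefficient means

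*Protocol article*

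**What the plan says.** All references are to the protocol article.

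- **Discussion (aim).** The study is meant to show that "the impact of hyperglycaemia at the time of recanalisation is a critical modifiable prognostic factor".
- **Introduction (hypothesis).** Patients below 155 mg/dL "during MT and especially at the time of reperfusion will have less ischaemia-reperfusion injury". The Introduction also contrasts the study with earlier work that relied on single readings, on admission or at 24 to 48 hours.
- **Abstract (aim).** The wording is milder: to evaluate an association between glucose during reperfusion and recovery at 3 months.
- **Statistical analysis.** Logistic regression is used "to evaluate the effect of glucose levels at the time of reperfusion on functional recovery at 3 months". Covariates are chosen by a rule and not by name; the rule is "adjusting for other factors that show statistically significant differences in the univariate analysis". Significance is judged by the likelihood ratio.
- **Data collection and management.** Emergency department values include "temperature, blood pressure, heart rate, respiratory rate, blood glucose and glycated haemoglobin". Diabetes and the time above 155 mg/dL before recanalisation are also recorded.
- **Sample size estimates.** 50 patients per group, from an unadjusted comparison of death or dependence.

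**The concern.** The claim is about timing, and admission glucose is its natural comparator. Reperfusion glucose is measured soon after admission glucose in the same patient, so the two are likely to be correlated. A reperfusion coefficient from a model without admission glucose would also be positive if hyperglycaemia at presentation were all that mattered.

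The covariate rule does not settle whether admission glucose is in the model. It may be treated as one of the other factors and screened, or as another measure of the exposure and never offered to the screen. If screened, its entry depends on its own p-value. The headline coefficient therefore has two possible meanings: the total association of reperfusion glucose with outcome, or its added value over admission glucose. Only the second bears on the recanalisation-specific claim, and with it on what monitoring during the procedure adds to a reading on arrival.

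The word modifiable raises a separate point. The study is observational, insulin is given at the attending physician's discretion, and the Introduction itself says it is not yet known whether insulin before and during thrombectomy lessens the harm.

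**Working it through.** **1. The plan's own figure.** Inputs from Sample size estimates: control rate 0.66, difference 0.30 (read as absolute, giving 0.36), alpha 0.05 (taken as two-sided), power 0.80, loss 15%.

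n = [1.96·√(2·0.51·0.49) + 0.842·√(0.66·0.34 + 0.36·0.64)]² / 0.30² = (1.386 + 0.568)² / 0.09 = 42.4, so 43 per group.

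Allowing for loss: 43/0.85 = 50.6, or 43·1.15 = 49.5. The stated 50 per group reproduces. It contains no allowance for adjustment. Evaluable patients: 100·0.85 = 85.

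**2. Only admission glucose matters.** Simulation with 85 patients, both glucose values on the SD scale, odds ratio 1.84 per SD of admission glucose, no other covariates, likelihood-ratio tests at 0.05, 4,000 runs per row. The odds ratio and the correlation r are assumptions; the article gives neither.

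| r | Reperfusion glucose significant, admission glucose left out | Same, univariate screen applied to admission glucose |
|---|---|---|
| 0.6 | 36% | 6.0% |
| 0.7 | 46% | 6.8% |
| 0.8 | 58% | 6.4% |
| 0.9 | 67% | 7.5% |

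Repeated runs put the middle column between 35% and 69% overall. Admission glucose passes the screen in 76% to 78% of runs. When it is always in the model, the rate is about 5% to 6%.

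With a larger effect (log odds ratio 0.85, about a 30-point gap at a median split), the rate without admission glucose is 40%, 69%, 81% and 91% at r = 0.5, 0.7, 0.8 and 0.9. Under the screen it is about 5% to 6%, with admission glucose entering in about 95% of runs.

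**3. Only reperfusion glucose matters.** With odds ratio 1.84 per SD of reperfusion glucose, admission glucose passes the screen in about 36% (r = 0.6) to 67% (r = 0.9) of runs. So even when the study's hypothesis is true, which of the two quantities is reported varies from one sample to the next.

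**4. Power of the separating test.** With one predictor, power at odds ratio 1.84 and 85 patients is about 0.77, so the expected z is about 1.96 + 0.74 = 2.70. Adding a covariate with correlation r multiplies this by √(1 − r²):

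| r | √(1 − r²) | Expected z | Approximate power | Simulated power |
|---|---|---|---|---|
| 0.6 | 0.80 | 2.16 | 0.58 | 0.58 |
| 0.7 | 0.71 | 1.93 | 0.49 | 0.50 |
| 0.8 | 0.60 | 1.62 | 0.37 | 0.36 |
| 0.9 | 0.44 | 1.18 | 0.22 | 0.22 |

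Starting instead from the plan's own design power of 0.80 gives 0.61, 0.52, 0.39 and 0.23. To hold 80% power, enrolment would have to be 100/(1 − r²): 157, 197, 278 and 527.

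**The case against.** A reader might infer that the plan never tests reperfusion glucose against admission glucose and cannot tell them apart, or that 35% to 69% is the false-positive rate of the plan as written. The article supports neither. Admission glucose is recorded, and on the ordinary reading of the covariate rule it is a candidate. If it is prognostic it usually enters, the likelihood-ratio assessment then becomes the nested test, and the false-positive rate is about 6% to 7%. The higher range applies only if admission glucose is kept out, which no section says.

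Three further points deserve weight. The Abstract states the aim as an association, which the model does address, so part of the conflict is wording in the Discussion and the hypothesis. A full protocol or analysis plan, not shown, could name the covariates. And a test with power between 0.58 and 0.22 will often be null even if reperfusion glucose truly matters.

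What remains is narrower. The article is not silent on covariates: it states a selection rule, and that rule leaves the meaning of the main coefficient to a p-value while the Discussion makes a timing claim. Low power is a reason to report the nested test as imprecise. It is not a reason to rest the timing claim on a model that may omit the comparator.

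On modifiability, the Introduction uses the word as background and admits the open question about insulin. The objection is therefore to the Discussion's stated intention to demonstrate it.

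**Conclusion.** The point holds in limited form. The recanalisation-specific aim has no prespecified analysis behind it. Whether the reperfusion coefficient is a total association or added value over admission glucose depends on an unstated choice of candidates and then on a significance screen.

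If admission glucose is left out, a misleading positive result occurs in about 35% to 69% of studies in which only admission glucose matters. If it is screened, the rate is about 6% to 7%, and the remaining problem is interpretation more than false positives. These figures rest on 85 evaluable patients, an assumed odds ratio of 1.84 per SD, an assumed correlation of 0.6 to 0.9 and no other covariates.

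The stated sample size is not in dispute; it reproduces for the unadjusted comparison. This is an inexpensive improvement and does not invalidate the association analysis.

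**What to change.** 1. Keep the planned model as the analysis of association, and state whether admission glucose is a candidate covariate in it.
2. Prespecify a secondary likelihood-ratio test: a model that always contains admission blood glucose and HbA1c or diabetes, against the same model plus reperfusion glucose. Report the adjusted odds ratio with its confidence interval.
3. State beforehand that this test is imprecise: power about 0.58, 0.50, 0.36 and 0.22 at r = 0.6, 0.7, 0.8 and 0.9 under the assumptions above, and possibly less once HbA1c or diabetes is also in the model. A null result does not refute the hypothesis. Report the observed correlation.
4. Claim a recanalisation-specific effect only if this test supports it. Otherwise conclude that peri-procedural glucose is associated with outcome.
5. Describe glucose as potentially modifiable, because the design is observational.

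The cost is one extra model on data already collected, no additional patients, and a secondary estimate with a wide interval.
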